#### Primary outcome

The scientific rationale is that the establishment of return-to-work (RTW) experts for inpatient mental health patients focuses on the workplace needs of these patients, leading to a better usage of existing resources as part of a work-related discharge management, and thus to a more successful return to the workplace.

The primary objective is to display this improved return to the workplace after in-patient psychiatric care as a group difference (intervention vs. control) using days in work and days of incapacity to work during 1 year after discharge from hospital.

#### Secondary outcomes

As outlined above an improved return to work following an in-patient psychiatric care treatment of patients may also result in a shorter period of **time to return to work** (partial/full), lower **termination rates** (both sides), a higher **quality of life** (EQ-5D, [20]), a higher **social functional level** (Mini-ICF-APP, [21]; Global Assessment of Functioning (GAF), [22]), a higher **job satisfaction** (German version of the Copenhagen psychosocial questionnaire (COPSOQ), [23]), a different **perception of stigmatization** (Self-stigma of mental illness scale – short form – subscale self-concurrence, [24]; Cognitive appraisal of stigma-related stress, [25]), lower **decisional conflict in regard to disclosure of the mental illness** (Decisional conflict Scale, [26]) and probable reduced **relapse rates**.

The basis for estimating the **cost of the illness** and the **health economic evaluation** of the RTW intervention are the medical and psychosocial health services made use of by the subjects and the number of days of incapacity for work for the whole study period.

The days of incapacity to work of the patients are on the one hand directly requested by the patients and their practitioners. It is envisaged that the patient’s details will be checked against those of some health insurance companies in order to assess the extent to which the data match.

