### Acute psychiatric crises, inpatient treatment and return to work

A particularly vulnerable time is that of an acute mental health crisis, which requires inpatient hospital treatment. It tears those affected out of their employment relationships, sometimes over longer periods of time. A successful reintegration of those patients after the acute episode of illness would therefore be an important prognostic factor for the further course of the disease. A failed reintegration in contrast would be a high risk factor for longer incapacity to work, long payment of sickness benefit, unemployment and a less favourable course of the disease.

Present data shows that it is a frequent health (or social) problem. In 2010 about 800,000 psychiatric inpatient cases were documented in Germany [13]. About 20% (= 160,000 people) of these cases were working patients [14]. Up to 30% of these patients did not return to work after discharge from hospital [14] and of those returning it was unclear how long they were able to successfully resume their employment relationships. Considering the related social decline and associated reduction in participation in social life, these numbers are alarming [15, 16].

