**Fig. 1 Fig1:**
[figure not shown]
German terms and their translation: BEM = Betriebliches Eingliederungsmanagement (Corporate integration management), Stufenweise Wiedereingliederung (gradual reintegration)

We expect improvements in the number of patients who will be able to return to work and also in the number of days at work in the year after release from hospital. This could also result in substantial economic savings (for example, sickness benefit, loss of productivity, etc.). Mediators of these expected improvements are increased numbers of patients for whom specific supportive measures (e.g., work therapy, gradual reintegration, BEM processes, etc.) are initiated. We assume that the proposed intervention primarily will increase the implementation of measures already existing in routine care and will help to overcome the interface problem at the time of inpatient discharge.

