#### Inclusion criteria

· Age 18–60 years.

· Diagnosis of a mental illness [ICD-10 Chapter F2–4, F6 (we assume that the majority of patients with existing employment relationships suffer from an affective disease [14]).

· In a contractual employment relationship, in which they can be reintegrated.

· Psychopathologically capable of reflecting on work in general and on their own work.

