### Data collection

The same data at the same time points will be collected in the intervention and control group (Table 1). Data collection will take place at five times during the inpatient stay and after discharge.

**Table 1 Tab1:** Planned data collection

	T0 (shortly after admission to hospital)	T1 (shortly before release from hospital)	T2 (3 months after release)	T3 (6months after release)	T4 (12 months after release)
Patient					
Demographics including information on					
School and vocational training	x				
Employment relationsship	x				
Business, enterprise (industry)	x				
Business, enterprise (size)	x				
Motivation	x	x	x	x	x
Anxiety, confidence	x	x			
Days of incapacity to work	x		x	x	x
COPSOQ	x			x	
COPSOQ (additional information)	x				
Self-stigma of mental illness scale short form – self-concurrence	x	x		x	
Cognitive appraisal of stigma-related stress	x	x		x	
Questions concerning disclosure of the disease at the workplace including					
Questions on the decision-making phase	x	x		x	
Questions on the decision to disclose	x	x		x	
Questions on the attitude towards disclosure	x	x		x	
Decisional Conflict scale	x	x		x	
Cognitive performance level		x			
CSSRI	x	x	x	x	x
Preparation of the return through the hospital		x			
Preparation of the return through the employer		x			
Preparation of the return through the RTW expert (intervention group only)		x		x	
Questions on the existing help network		x		x	x
Content of the employer support				x	
Evaluation of the employer support				x	
Evaluation of the RTW expert support (intervention group only)				x	
EuroQOL - Gesundheitsbarometer	x	x		x	
EQ-5D		x		x	x
Self-efficacy expectation (RTW-SE)		x			
Resilience (RS-13)					x
Patient Health Questionnaire (PHQ-D)		x			
Days at work			x	x	x
Days of incapacity for work			x	x	x
Days of partial return to work			x	x	x
Questions on discrimination at the workplace				x	
Coping				x	
Attending physician					
CGI	x	x			x
GAF	x	x			x
ICD Diagnosis and medical history	x	x			x
HoNOS		x			
Prediction on return to work		x			
RTW expert (intervention group only)					
Type and scope of workplace-related support		x		x	
Evaluation of workplace-related support		x		x	
Prediction on return to work		x			
Quality of relationship		x		x	
Return to work				x	
Questions concerning the use of communication media				x	
Open summary				x	

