### Sample size calculation and statistical analysis

The aim is to obtain a sample of *n* = 28 clusters (i.e. psychiatric acute wards) with a total of 200 patients (8–10 per cluster). For this, about 2000 patients need to be screened (Mernyi et al., 2018).

In order to be able to demonstrate a significant result with a power of 80% assuming a small to medium effect size (0.5), a total sample size of 128 patients is required (two-sided independent samples t-test, α = 0.05). With regard to expected drop-outs (drop-out rate 30–40%), this minimum number of cases is planned to be exceeded by 72 patients. Thus, a total of 200 patients are to be included (100 in each group).

The primary analysis will be a comparison of days in work at T4 between the intervention and control groups. To assess the effect of the intervention on the continuous primary outcome, a random effects linear regression model will be fitted with ward (cluster) as a random effect term and intervention group as a fixed effect. The point estimate for the intervention effect will be reported together with the corresponding 95% confidence interval. A *p*-value < 0.05 will be considered as providing statistical significant evidence of a group difference. A per protocol approach will be taken to the analysis, i.e. patients in intervention clusters will be analyzed in this group, if they had contact with the RTW-expert at least once during their inpatient stay and once after discharge.

Exploratory analyses will be performed to assess the effect of the intervention on the secondary outcome measures. Random effect linear models will be fitted to the continuous secondary outcome measures, analogous to the primary analysis. For binary secondary outcome measures, logistic regression models using GEEs will be fitted.

The health economic analysis is based on the net benefit approach. To analyze the cost-effectiveness of the RWT intervention, the incremental cost-effectiveness ratio (ICER) is determined for gaining a QALY compared to routine treatment. The estimation of ICER stochastic uncertainty is done by nonparametric bootstrapping and the determination of the cost-effectiveness acceptance curve [29].

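### The 6-month COPSOQ comparison is conditional on still having a job, which the intervention is meant to change, so the planned model of arm does not estimate a randomised effect on job satisfaction

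*Protocol article*

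**What the plan says.** The Secondary outcomes section of the protocol article lists higher job satisfaction among the expected benefits and names the instrument: "German version of the Copenhagen psychosocial questionnaire (COPSOQ"). The same sentence also expects "lower termination rates (both sides").

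Table 1 (Data collection) marks COPSOQ at "T0 (shortly after admission to hospital") and, after discharge, only at "T3 (6months after release"). At T0 all patients have a job on paper, because the inclusion criteria require them to be "In a contractual employment relationship, in which they can be reintegrated".

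On return to work, the text under Fig. 1 states: "We expect improvements in the number of patients who will be able to return to work". The Background gives a figure for working psychiatric inpatients in general: "Up to 30% of these patients did not return to work after discharge from hospital". No time point is attached to it.

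The section on sample size and statistical analysis fixes the model: "Random effect linear models will be fitted to the continuous secondary outcome measures, analogous to the primary analysis". The primary model has ward as a random effect and intervention group as a fixed effect. The same section calls the secondary analyses exploratory.

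**The concern.** Job satisfaction exists only for someone who has a job. At T3 some patients will have lost theirs, and others will hold a contract without working under it. The first group has no current job to rate. The second can answer, but the answer describes a job not currently being done. Both states arise after randomisation, and the protocol predicts that both will be less common in the intervention arm.

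A linear model of arm uses only patients with a score. It therefore compares selected parts of the two arms, and the selection differs by arm if the intervention works. This is not ordinary drop-out. For a patient without a job the value does not exist, so imputation does not restore the randomised comparison.

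Suppose the RTW experts keep in work some patients who would otherwise have lost their jobs, and these patients tend to be less satisfied. Mean satisfaction among scored patients then falls in the intervention arm even if no individual's satisfaction has changed. A reader could wrongly conclude that the intervention returns people to worse jobs, or a modest real benefit could be hidden.

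**Working it through.** **The plan's own figure.** The article gives no figure for COPSOQ. Its sample size is for the primary outcome: effect size 0.5, two-sided α = 0.05, power 80%. The exact t-test calculation gives 63.77, so 64 per arm and 128 in total, as stated. This neither supports nor refutes the point; 64 per arm is used below only to express bias in standard errors.

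**Method.** Let a standard normal trait Z be the propensity to keep a job (or to return). The share p with the highest Z has a score. Satisfaction, in SD units, correlates r with Z, and the true effect of the intervention on satisfaction is zero.

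- Mean of Z among scored patients: m(p) = φ(z)/p, where z is the (1 − p) quantile of the standard normal.
- Bias = r × [m(p in intervention) − m(p in control)].
- SE = √(1/(64 p in control) + 1/(64 p in intervention)), ignoring clustering.

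**Inputs.** Only the 70% has a source in the article: up to 30% not returning implies about 70% or more returning without the intervention. All other shares, r = 0.3 to 0.5 and its positive sign are assumptions. In two of the rows the intervention share comes from reading 0.5 as a shift in Z, which is also an assumption: Φ(0.524 + 0.5) = 0.847 from 70%, and Φ(0.253 + 0.5) = 0.774 from 60%.

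**Values of m(p).** 0.60: 0.644; 0.70: 0.497; 0.774: 0.388; 0.80: 0.350; 0.847: 0.279; 0.85: 0.274; 0.90: 0.195; 0.95: 0.109.

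| Who lacks a score at T3 | Control vs intervention scored | Difference in m | Bias, r = 0.3 | Bias, r = 0.5 | SE | Bias in SE |
|---|---|---|---|---|---|---|
| Ended contracts only | 90% vs 95% | -0.086 | -0.03 SD | -0.04 SD | 0.184 | 0.1 to 0.2 |
| Ended contracts only | 85% vs 95% | -0.166 | -0.05 SD | -0.08 SD | 0.187 | 0.3 to 0.4 |
| All non-returners | 70% vs 80% | -0.147 | -0.04 SD | -0.07 SD | 0.205 | 0.2 to 0.4 |
| All non-returners | 70% vs 84.7% | -0.218 | -0.07 SD | -0.11 SD | 0.202 | 0.3 to 0.5 |
| All non-returners | 60% vs 77.4% | -0.256 | -0.08 SD | -0.13 SD | 0.215 | 0.4 to 0.6 |

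The first two rows fit the article better, because T0 shows that contract holders who are not at work are asked to complete COPSOQ. The last three are the wider case, in which every patient not back at work lacks a score. If r were negative, every sign in the table would reverse.

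**The case against.** A reader might infer that COPSOQ can be scored only for patients who are back at work. The article does not say so, and Table 1 points the other way: at T0 the questionnaire goes to inpatients who hold a contract but are not working. A patient on sick leave at T3 is in the same position. Only ended employment clearly removes a score, and the article gives no termination rate. This objection stands, and it limits the firm part of the point to ended contracts.

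A reader might also turn the 30% into a count of patients without a valid T3 score. That is not supported either. The figure is an upper bound on non-return in a background population, with no stated time, and not a rate of job loss at 6 months.

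Nor does it follow that success on the primary outcome must look like harm here. The correlation, its sign and the difference between arms are all assumed, and even the larger values are a fraction of a standard error. The outcome is exploratory.

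Finally, this is a condensed article and no analysis plan is shown, so the absence of a scoring rule is not itself a fault. What remains is the model that the article does fix for all continuous secondary outcomes. Applied to T3 COPSOQ as written, it yields a comparison conditional on a result of treatment, whatever scoring rule a fuller document adds for patients who have a job.

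**Conclusion.** The point holds as a limited one. The planned arm comparison of T3 COPSOQ is conditional on employment, which the protocol expects the intervention to change, so it is not a randomised estimate of the effect on job satisfaction. It may be biased, possibly against an effective intervention.

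With zero true effect and r between 0.3 and 0.5, the illustration gives about -0.03 to -0.08 SD if ended contracts alone select, and about -0.04 to -0.13 SD if all non-returners lack a score. Direction and size depend on those assumptions. No confirmatory conclusion is affected; what changes is how the job-satisfaction result may be read.

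**What to change.** In the statistical analysis section, take COPSOQ job satisfaction out of the general sentence on continuous secondary outcomes and state:

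- T3 COPSOQ is analysed among patients who still have a job at T3, with the same random-effects model, adjusted for T0 COPSOQ.
- The numbers employed, at work and scored at T3 are reported beside it, by arm.
- The result is labelled as conditional on employment and not as a randomised estimate of the intervention's effect on satisfaction.

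A composite that ranks or counts having no job as the worst outcome may be added as a sensitivity analysis. It partly repeats return to work, which the primary outcome already covers, so a difference on it would say little about satisfaction alone.

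The cost is small. COPSOQ at T0 and T3 and days at work at T3 are already collected in both arms. One item needs checking: Table 1 lists the employment relationship at T0 only, and the T3 return-to-work item comes from the RTW expert in the intervention arm only. Employment status at T3 should therefore be taken in both arms from the data used for termination rates. Adjustment for T0 COPSOQ removes only the part of the selection that baseline satisfaction explains. The downside is that the job-satisfaction result can no longer be read as a causal effect of arm.

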#### Qualitative data

To generate a better understanding of the return-to-work process and potential mechanisms of the intervention qualitative data will also be obtained. The evaluation uses multiple instruments and a mixed-methods design: Face-to-face, audio-taped, semi-structured interviews (individual and focus groups) and analysis of medical records and RTW-expert documentation. The survey involves patients (approx. *n* = 20) and as far as possible all staff members who are concerned with the daily practices of return to work (e.g. return-to-work-experts, social worker, physicians, psychologists). Data collection, data analysis and theoretical development will be based on the fundamental process of the grounded theory. Among other things, this includes theoretical sampling, the coding of the data and the application of the coding paradigm [27, 28].

### Treatment adherence

To assess treatment adherence, we will document whether all patients got an RTW intervention, the contact frequency, to what extent single units of the intervention were implemented for a patient (i.e. coaching sessions) and what the RTW experts did. In addition, we will use a qualitative approach in the intervention group to assess various aspects of the process of RETURN as well as barriers and facilitators of RETURN.

### Sample size calculation and statistical analysis

The aim is to obtain a sample of *n* = 28 clusters (i.e. psychiatric acute wards) with a total of 200 patients (8–10 per cluster). For this, about 2000 patients need to be screened (Mernyi et al., 2018).

In order to be able to demonstrate a significant result with a power of 80% assuming a small to medium effect size (0.5), a total sample size of 128 patients is required (two-sided independent samples t-test, α = 0.05). With regard to expected drop-outs (drop-out rate 30–40%), this minimum number of cases is planned to be exceeded by 72 patients. Thus, a total of 200 patients are to be included (100 in each group).

The primary analysis will be a comparison of days in work at T4 between the intervention and control groups. To assess the effect of the intervention on the continuous primary outcome, a random effects linear regression model will be fitted with ward (cluster) as a random effect term and intervention group as a fixed effect. The point estimate for the intervention effect will be reported together with the corresponding 95% confidence interval. A *p*-value < 0.05 will be considered as providing statistical significant evidence of a group difference. A per protocol approach will be taken to the analysis, i.e. patients in intervention clusters will be analyzed in this group, if they had contact with the RTW-expert at least once during their inpatient stay and once after discharge.

Exploratory analyses will be performed to assess the effect of the intervention on the secondary outcome measures. Random effect linear models will be fitted to the continuous secondary outcome measures, analogous to the primary analysis. For binary secondary outcome measures, logistic regression models using GEEs will be fitted.

The health economic analysis is based on the net benefit approach. To analyze the cost-effectiveness of the RWT intervention, the incremental cost-effectiveness ratio (ICER) is determined for gaining a QALY compared to routine treatment. The estimation of ICER stochastic uncertainty is done by nonparametric bootstrapping and the determination of the cost-effectiveness acceptance curve [29].

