#### Randomization and blinding

We will determine pairs of comparable wards (number of patients, distribution of diagnoses, staff etc.) and then randomize one ward of each pair to the intervention and one ward to the control condition. While the principal investigators will determine the paired wards, the statistical institute of our department (IMedIS) will do the randomization.

Randomization takes place at cluster level (*n* = 14 wards each to the intervention group or control group) to minimize contamination effects [19].

As to the nature of the intervention (implementation of RTW-experts) there will be no blinding.

To avoid selection bias, all patients fulfilling inclusion criteria will be recruited consecutively in the intervention and control group. This process is monitored by the study center and will be reported in form of a CONSORT diagram. There will be special emphasis on documenting how many patients (and for what reasons) did not consent to participate in the trial.

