## Discussion

There has been an increasing awareness of the interplay between work and mental health in recent years. However, the group of patients suffering from (severe) mental illnesses that require hospitalization and their potential return to their workplaces has been neglected. The RETURN study aims to establish and evaluate a pragmatic intervention that may improve the return to work process of these patients.

This approach is already internationally established in the field of somatic rehabilitation and supported employment [30–32]; the innovative aspect of this project is to implement and evaluate it in standard psychiatric care in Germany. This project requires no new interventions to be developed and tested, as the techniques of the case manager/job coach is applied to the field of return to work.

The inclusion of patients with severe mental illnesses (including those with schizophrenia, bipolar disorder, borderline personality etc.), the controlled design with cluster randomization and the duration of the follow-up period are methodical strengths. In addition, we intend to use a broad recruitment basis (the great majority of psychiatric hospitals in the greater Munich area) to enhance the generalizability of the results. Finally, the mixed-methods approach will allow deep insight into potential barriers and facilitators of the implementation of our intervention.

The heterogeneity of the participants with regard to diagnoses, illness severity and working environment as well as the settings (open vs. closed wards, specialized vs. non-specialized wards) could limit the significance of the results. In addition, the special feature of the study – an intervention in the form of a case management that focuses on work - can only be standardized to a certain extent.

To conclude we expect the RTW-experts to better focus inpatient treatment on the specific needs of patients who are still competitively employed and thereby improve return to work patterns.

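### The sample size treats patients as independent although wards are randomised, so the stated 80% power for 0.5 SD is overstated

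*Protocol article*

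**What the plan says.** The section on sample size and statistical analysis in the protocol article gives the whole calculation. The target is a significant result "with a power of 80% assuming a small to medium effect size (0.5"), for which "a total sample size of 128 patients is required (two-sided independent samples t-test, α = 0.05"). The step from 128 to 200 has one stated reason: "With regard to expected drop-outs (drop-out rate 30–40%), this minimum number of cases is planned to be exceeded by 72 patients". The conclusion is: "Thus, a total of 200 patients are to be included (100 in each group").

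The design is clustered. Under Randomization and blinding: "Randomization takes place at cluster level", with 14 wards per arm. The planned primary analysis follows that design: "a random effects linear regression model will be fitted with ward (cluster) as a random effect term and intervention group as a fixed effect". The recruitment target is given as "28 clusters (i.e. psychiatric acute wards) with a total of 200 patients (8–10 per cluster").

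**The concern.** The test used to size the trial is not the analysis planned for it. An independent-samples t-test assumes that two patients on the same ward are no more alike than two on different wards. When wards are randomised, any between-ward variation in days at work adds to the variance of the treatment contrast, and the ward random effect will carry that into the standard error.

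An ICC of zero is hard to defend here. The Discussion names variation between wards as a limitation: "the settings (open vs. closed wards, specialized vs. non-specialized wards) could limit the significance of the results".

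The 80% figure is what funders and readers will use to interpret the result. If power for 0.5 SD is nearer 70%, a non-significant result will be given more weight as evidence against such an effect than it deserves.

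**Working it through.** **Inputs from the protocol article.** Two-sided α = 0.05; power 80%; d = 0.5; 1:1 allocation; 200 enrolled; drop-out 30–40%; 28 wards.

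**Assumptions.** The ICC is not in the document; a range of 0.01 to 0.10 is shown. Wards are taken as equal in size, and d is expressed in units of the total SD.

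**1. Reproduce the plan's figure.** For a two-sample t-test with 64 per arm, the noncentrality is 0.5 × √(64/2) = 2.83. With 126 degrees of freedom (df) the power is 80.1%; 63 per arm gives 79.5%. So 128 is exactly the requirement for independent patients.

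**2. See what the extra 72 patients cover.** 72/200 = 36%, and 200 × (1 − 0.36) = 128. Over the stated drop-out range:
- 30%: 200 × 0.70 = 140 analysed
- 36%: 128 analysed
- 40%: 200 × 0.60 = 120 analysed

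**3. Apply the clustering.** The design effect is DE = 1 + (m − 1) × ICC, with m = analysed N / 28, and the effective sample size is N / DE. For N = 128, m = 128/28 = 4.57. At ICC 0.05, DE = 1 + 3.57 × 0.05 = 1.18, the effective N is 128/1.179 = 108.6, and the noncentrality is 0.5 × √(54.3/2) = 2.61.

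Power is from the noncentral t distribution, first with patient-level df (N − 2), then with ward-level df (28 − 2 = 26):

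| Analysed N | ICC | DE | Effective N | Power, df N − 2 | Power, df 26 |
|---|---|---|---|---|---|
| 128 | 0.01 | 1.04 | 123.6 | 78.8% | 76.3% |
| 128 | 0.02 | 1.07 | 119.5 | 77.4% | 74.9% |
| 128 | 0.05 | 1.18 | 108.6 | 73.4% | 70.8% |
| 128 | 0.10 | 1.36 | 94.3 | 67.3% | 64.7% |
| 140 (30% drop-out) | 0.02 | 1.08 | 129.6 | 80.7% | 78.2% |
| 140 (30% drop-out) | 0.05 | 1.20 | 116.7 | 76.5% | 73.9% |
| 120 (40% drop-out) | 0 | 1.00 | 120.0 | 77.5% | 75.1% |
| 120 (40% drop-out) | 0.05 | 1.16 | 103.1 | 71.1% | 68.6% |

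**4. Detectable effect.** With 128 analysed and ICC 0.05, 80% power is reached at 0.54 SD (df 126) or 0.56 SD (df 26).

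**5. What 80% for 0.5 SD would need.** With 28 wards and ICC 0.05, 158 analysed patients (df N − 2) or 170 (df 26). At 30% drop-out that is 226 or 243 enrolled; at 40%, 264 or 284.

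**The case against.** **The wards are small, so the loss may be small.** This is true at the low end. With 128 analysed and patient-level df, the loss is 1 to 3 points at ICC 0.01–0.02. It becomes material from about 0.05, and nothing in the article says which value applies. The Discussion does not quantify between-ward variation, and part of the heterogeneity it lists is between patients.

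**At 30% drop-out there is a reserve of 12 patients.** This also stands. With 140 analysed, 80% holds up to an ICC of about 0.025 with patient-level df, but only to about 0.008 with 26 df. At 40% drop-out, power is below 80% before any clustering, so part of that shortfall comes from drop-out.

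**Wards are paired, which should remove some between-ward variation.** It may, but the stated primary model names no pair term and the calculation takes no credit for pairing.

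**Eight to ten patients per ward would supply more than 200.** 28 × 8 = 224 and 28 × 10 = 280, whereas 200/28 = 7.1. With 224 enrolled and ICC 0.05, power is about 80% at 30% drop-out and 75% at 40% (78% and 72% with 26 df). But the calculation concludes with 200, so this is an inconsistency to resolve rather than a margin to rely on.

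**The analysis itself remains valid.** Agreed: ward is in the model and a 95% confidence interval is planned. The fault lies in the power claim, not in the inference.

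**Conclusion.** The point holds. The arithmetic behind 128 is right, but it belongs to a different design, and the article's own steps close at 200 with no term for clustering. This is not a detail left to a fuller document.

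The size rests on an assumed ICC. Over 0.02 to 0.10 with 128 analysed, power is 77% to 67%, about 2.5 points less with ward-level df. The stated 80% survives only when drop-out is near 30% and the ICC is close to zero. Two features not in these figures would lower power further: unequal ward sizes (an assumed coefficient of variation of 0.65 at ICC 0.05 gives 70.0% instead of 73.4%) and the per-protocol rule that removes intervention patients without both contacts. A pair term or baseline covariates in the model could recover some of the loss.

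**What to change.** Keep the 28 wards and 200 patients, and replace the t-test statement with a cluster calculation. It should state:
- the number analysed per ward at both 30% and 40% drop-out;
- an assumed ICC with its source and a range;
- the design effect, with an allowance for unequal ward sizes;
- the degrees of freedom used;
- the resulting power for 0.5 SD, or the effect detectable with 80% power.

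For example: with 128 analysed and an assumed ICC of 0.05, power for 0.5 SD is 71–73%, and 80% power is reached at 0.54–0.56 SD. Credit for the ward pairs or baseline (T0) covariates may be taken if they are entered in the primary model. The same paragraph should reconcile 8–10 patients per ward with a total of 200.

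The cost is a rewritten paragraph and a less favourable figure. No extra patients or wards are needed unless the sponsor wants to keep 80% power for 0.5 SD.

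### 28 wards at 8–10 patients each do not give 200, and the 72-patient allowance covers drop-out only up to 36% of the stated 30–40%

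*Protocol article*

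**What the plan says.** All the figures stand in one section of the Protocol article, Sample size calculation and statistical analysis.

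- **Clusters and total.** The section aims at 28 wards "with a total of 200 patients (8–10 per cluster").
- **Analysed number.** For 80% power, "assuming a small to medium effect size (0.5"), it states that "a total sample size of 128 patients is required (two-sided independent samples t-test, α = 0.05").
- **Drop-out.** "With regard to expected drop-outs (drop-out rate 30–40%), this minimum number of cases is planned to be exceeded by 72 patients". The total is then set at 200, with 100 per group.

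The count of 28 wards (14 per arm) appears also in the Abstract, in Setting and participants and in Randomization and blinding. The total of 200 appears also in the Abstract. The article names no single planning rate within 30–40%, does not define drop-out, and does not explain the 8–10 per ward.

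**The concern.** The number of wards, the patients per ward and the total are tied by one multiplication, and here they do not multiply out. Someone running recruitment cannot tell which figure governs. Wards that each recruit 8 to 10 will overshoot 200; stopping at 200 leaves the average ward below 8.

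The drop-out allowance is a single number set against a range. If that number does not reach the top of the range, the analysed sample can fall below what the plan itself calls its minimum while drop-out stays within what the plan expects. The 80% power would then not hold over the whole range for which it appears to be claimed.

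**Working it through.** **Inputs**, all from the section Sample size calculation and statistical analysis: standardised effect 0.5; two-sided α = 0.05; independent samples t-test; power 80%; 128 required; drop-out 30–40%; allowance 72; total 200 in two equal groups; 28 wards; 8–10 patients per ward.

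**1. Reproduce the 128.** Solving the two-sample t-test for 80% power at effect 0.5 gives 63.8 per group, so 64 per group and 128 in total. Power at 64 per group is 80.1%. The stated figure is correct for the stated test.

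**2. Reproduce the 200.** The implied drop-out is 72 / 200 = 36%, and 128 / (1 − 0.36) = 200 exactly. The inflation formula is the right one. The mistaken form, 128 × (1 + d), would give only 167 to 180 over the range.

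**3. Go over the stated drop-out range.** Enrolment needed to keep 128 is 128 / (1 − d), rounded up. The number left from 200 is 200 × (1 − d). Power is by the plan's t-test at effect 0.5, with equal groups.

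| Drop-out d | Enrolment needed for 128 | Analysed out of 200 | Power |
|---|---|---|---|
| 30% | 128 / 0.70 = 182.9, so 183 | 140 | 83.6% |
| 35% | 128 / 0.65 = 196.9, so 197 | 130 | 80.8% |
| 36% | 128 / 0.64 = 200 | 128 | 80.1% |
| 40% | 128 / 0.60 = 213.3, so 214 | 120 | 77.5% |

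So 200 is enough from 30% up to 36% and short above 36%. At 40% it is short by 214 − 200 = 14 enrolled patients, or 128 − 120 = 8 analysed patients.

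**4. Multiply out the wards.**

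- 28 × 8 = 224, and 28 × 10 = 280.
- The excess over 200 is 24 to 80 patients, or 12% to 40% of 200.
- 200 / 28 = 7.1 per ward.
- Read the other way, 200 patients at 8 to 10 per ward fill 200 / 10 = 20 to 200 / 8 = 25 wards, not 28.

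**5. Try the obvious alternative reading.** Suppose that 8–10 means patients left after drop-out. Then 120 to 140 completers over 28 wards give 120 / 28 = 4.3 to 140 / 28 = 5.0 per ward. This widens the gap.

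**6. See what the lowest ward figure would deliver.** With 8 per ward, 224 are enrolled. At 40% drop-out 224 × 0.60 = 134.4 remain, so 134, with power of about 82%. That total would keep more than 128 patients over the whole 30–40% range.

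**The case against.** **The drop-out allowance is a planning choice.** The article gives a range, and 200 is what 36% requires; the midpoint, 35%, needs 197. The formula is correct, 30% leaves 17 patients to spare (200 − 183), and the section does not promise 80% power at the worst end. This largely stands. A reader might infer that 200 fails the 30–40% range as a whole, and the figures do not support that: the shortfall exists only above 36%, and at 40% the loss is 80.1 − 77.5 = 2.6 percentage points. What remains is that the plan calls 128 a minimum, gives 40% as an expected rate, and falls below that minimum at that rate without saying so.

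**The per-ward figure is a side remark.** It feeds no calculation in the article, 200 and 28 are repeated consistently elsewhere, and a random-effects model accepts any ward size. With uneven recruitment some wards could well reach 8–10 within a total of 200. This is fair as to weight, and suggests that 8–10 is the figure out of line. It does not reconcile the numbers: the average over 28 wards is 7.1, and no reading of the text makes all three figures true.

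**Two further inferences are tempting and go too far.**

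- A reader might infer that patients excluded from the primary analysis for lacking the two contacts with the return-to-work expert reduce the sample on top of the 30–40%. Drop-out is not defined, so these patients may be counted in it already, and some will also be lost to follow-up. The article does not show that they are additional.
- A reader might use the ward size to argue a further loss of power through the design effect. The plan's calculation contains no design effect. Clustering is a separate point and adds nothing to this one.

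**Conclusion.** The point holds in two parts of unequal reach.

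The ward figures contradict each other outright: 28 wards at 8–10 patients is 224–280, while 200 is about 7 per ward. This rests on multiplication alone.

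The drop-out allowance is adequate up to 36% and inadequate from there to the plan's own upper figure of 40%, where 120 patients are analysed and power is 77.5%. This rests on the plan's own assumptions: effect 0.5, two-sided α = 0.05, an independent samples t-test, and equal groups after drop-out. Clustering is ignored, as in the plan.

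The loss of power is modest and does not undermine the design. The paragraph is nevertheless wrong as written on figures that recruitment and the power claim depend on, and it should be corrected.

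**What to change.** Keep 200 and replace 8–10 per ward by about 7 per ward (200 / 28). Replace the single power statement by power over the expected drop-out range, labelled as resting on the plan's t-test assumption: 83.6% at 30%, 80.1% at 36%, 77.5% at 40%.

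If 8 per ward is already the real recruitment target, correct the total to 224 instead, with 112 per group. At 40% drop-out this leaves 134 analysed patients and about 82% power on the same assumption.

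The first option costs a few corrected figures in one paragraph, and a stated power that is slightly less favourable at the upper end of the drop-out range. The second also means changing the total and group size wherever they are repeated, including the Abstract.
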